### Organ Retrieval

Organs are procured using the technique developed by Starzl. Following aortic clamping, abdominal organs are flushed in situ through the aorta and portal vein with cold Celsior solution, retrieved, dipped in a bag filled with preservation fluid, and stored on ice (1 L, livers; 0.5 L, kidneys). Pretransplant biopsies are performed according to our retrieval protocol.

Retrieved organs are stored on ice during the transfer from donor to the transplant hospital, during the biopsy analysis, until cross-matched results are returned, and until the final decision regarding donor and recipient eligibility.

#### Hypothermic Oxygenated Machine Perfusion

Organ perfusion is conducted with the Vitasmart (Medica, Bologna, Italy) machine, expressly designed for ex vivo perfusion of abdominal organs [7]. This machine system consists of two pumps, one heat exchanger, and three flow and pressure probes (Figure 2). The sterile disposable perfusion set is composed of a membrane oxygenator, tubing for vessel cannulation, and surgical cannulas.

Kidney perfusion is performed through the renal artery at a pressure of 25-30 mm Hg. Liver perfusion is performed through the portal vein at a pressure of 5 mm Hg.

Flow, pressure, and temperature are monitored and stored on a USB memory device during organ perfusion. Gas analysis of the effluent perfusate is accomplished at the start of perfusion (T0) and then every 30 minutes to determine carbon dioxide partial pressure, oxygen partial pressure (pO_2_), pH, and lactate levels. Two perfusate samples are collected at the beginning and at the end of perfusion to rule out bacterial or fungal contamination.

Graft perfusion is performed in the operating room, from the start of the back-table preparation to organ implantation. First, each organ is connected to the perfusion device through cannulation of the vessels with appropriately sized cannulas. HOPE starts by flushing the organ at low flow values (20 mL/min) with new oxygenated perfusion fluid during the back-table preparation, with the aim of removing waste products and residual microthrombi. After the back-table preparation is completed, the organ is treated with continuous HOPE until transplant. Organ perfusion is continuously monitored. As previously reported [7,8], minimal perfusion time is 1 hour for livers and 2 hours for kidneys.

Belzer machine perfusion solution (2 L, kidneys; 3 L, livers) at 4-10°C, in sterile conditions, and with continuous oxygenation (pO_2_ of 500-600 mm Hg) is used for perfusion.

#### Static Cold Storage

Livers/kidneys undergoing SCS are stored in sterile organ bags with Celsior solution and cooled on ice (0.5 L, kidneys; 1 L, livers).

### Transplantation, Immunosuppressive Therapy, and Management During Hospital Stay

KT and LT are performed according to the center’s standard techniques. Kidneys are implanted into either the iliac fossa with arterial anastomoses to the external, common, or internal iliac arteries or vein anastomoses to the external or common iliac veins and ureter-bladder anastomoses over a single stent. Livers are transplanted orthotopically preserving the inferior vena cava with a piggyback technique.

Postoperative management, including immunosuppression and antimicrobial, antifungal, and antithrombotic prophylaxis, follows the standard local protocol [15].

### Analyses of Outcomes

#### Liver Transplant Primary Outcome

The rate of EAD and the Liver Graft Assessment Following Transplantation (L-GrAFT) risk score [16,17] will be analyzed to evaluate the postoperative outcomes of the enrolled liver recipients (Figure 3).

EAD is defined by the presence of at least one of the following lab results: bilirubin >10 mg/dL, international normalized ratio >1.6 on postoperative day 7, ALT >2,000 IU/mL within the first 7 postoperative days, or AST >2,000 IU/mL within the first 7 postoperative days [17]. The L-GrAFT risk score is calculated from the peak AST level, bilirubin levels, platelet counts, and international normalized ratio values from days 1 to 10 post-LT [17].

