#### Randomization

Patients are randomized 1:1 to the HOPE and SCS groups according to the treatment list produced by the randomizer tool. For KT, patients are stratified according to the duration of CIT before HOPE starts (longer or shorter than 12 hours); grafts with CIT >20 hours are excluded from the study. For LT, patients are stratified according to the contemporary presence of ECD liver criteria (more or less than 5 criteria). The study information and informed consent form are distributed to potential recipients. Randomization is performed for patients who sign the consent form after the organ is deemed suitable for transplantation.

To favor comparison between paired kidneys, when both kidneys from the same donor are allocated to the same center, grafts are automatically assigned to a study group and the corresponding control group. Furthermore, in cases where there are multiple transplants occurring at the same time, we prioritize LT over KT, to reduce the CIT.

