### Statistical Analyses

#### Sample Size Calculation

The sample size was calculated using the primary outcomes of EAD and DGF for LT and KT, respectively, and the secondary outcomes of PNF and LHS, as reported in similar studies [11,19,20].

In particular, the rates of PNF and EAD are expected to decrease for the LT-HOPE group, thereby improving the postoperative course and LHS. We are expecting the following reductions in these parameters: PNF, 5% (HOPE) vs 10% (SCS); EAD, 10% (HOPE) vs 20% (SCS); and postoperative LHS <21 days, 80% (HOPE) vs 50% (SCS).

In KT, HOPE should reduce the rate of DGF from 50% to 30%, with a general improvement in the postintervention outcomes.

Based on these parameters, the total sample size was estimated at 220 patients, with distribution throughout the 4 groups as already explained (alpha=.05, two-sided test, power of 80%; calculated with nQuery Advisor 7.0, Statsols, Cork, Ireland).

The sample size was calculated to account for a dropout risk of 5-10% for the year.

A preliminary analysis will be performed when half of the enrollment is completed.

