#### Preliminary Analyses

To monitor and optimize the planned surgical and clinical procedures, real-time data analyses are performed before the final data collection. In detail, we are performing two interim analyses on the data from the first 7 posttransplant days. The primary analyses will be performed after the enrollment of 60 patients. The second analyses will be performed after the enrollment of 160 patients.

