#### Statistical Tests

The continuous variables will be compared using parametric (ANOVA) or non-parametric (Kruskal-Wallis) tests according to the data distribution, and the categorical variables will be compared using chi-squared tests. Multivariate analysis will be performed using forward stepwise logistic regression analysis. Survival analysis will be conducted using the Kaplan-Meier method. *P* values <.05 will be considered statistically significant.

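### EAD and L-GrAFT are both listed as the liver primary outcome, but the trial is sized on EAD alone and nothing says which decides; if either may count, the false-positive rate is about 8–9%, not 5%

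*Protocol article*

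**What the plan says.** Three places in the protocol article bear on this point.

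- **Liver Transplant Primary Outcome.** The heading is singular, but the text names two measures: "The rate of EAD and the Liver Graft Assessment Following Transplantation (L-GrAFT) risk score". EAD is a yes/no event in the first 7 postoperative days, built from bilirubin, INR, ALT and AST. L-GrAFT is a score built from AST, bilirubin, platelets and INR over days 1 to 10. The section gives no order between them and no rule for combining them.
- **Sample Size Calculation.** "The sample size was calculated using the primary outcomes of EAD and DGF for LT and KT, respectively". Here EAD is the liver primary. The secondary outcomes that fed into the calculation are also listed (PNF and length of stay), and L-GrAFT is not among them. The error rate is set in the same section: "alpha=.05, two-sided test, power of 80" percent.
- **Statistical Tests.** One threshold serves every comparison: P "values <.05 will be considered statistically significant".

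The Results section also mentions only EAD when it describes the expected benefit in liver recipients.

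**The concern.** The two sections give different sets of liver primary outcomes: EAD with L-GrAFT in one, EAD alone in the other. This affects the claim that the trial may make. With two measures under one primary heading and a flat P<.05, a significant result on either could be presented as a positive liver trial, and the 5% error rate would then not be held.

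The second problem is disagreement between the outcomes. At 55 livers per arm a non-significant EAD result is likely even if the assumed effect is real (see the power figure below). A significant L-GrAFT beside a non-significant EAD is therefore a realistic outcome, and the article does not say what the liver trial would then conclude. The trial is open-label and already recruiting, so the choice should be fixed before liver outcomes are compared by arm.

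**Working it through.** **Inputs from the article.** Two listed liver primaries; two-sided 5% per test; 55 livers per arm; EAD 20% on SCS and 10% on HOPE.

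**Assumed input.** The correlation ρ between the EAD and L-GrAFT test statistics. The article gives none, so a range is shown. It should be positive, because three of the four L-GrAFT inputs (AST, bilirubin, INR) also define EAD, over overlapping days.

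**1. The plan's own figure.** The article states no overall false-positive rate, so there is none to reproduce. The figure tied to its alpha is the sample size. For EAD:

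n per arm = [1.96 × √(2 × 0.15 × 0.85) + 0.8416 × √(0.20 × 0.80 + 0.10 × 0.90)]² / 0.10² = (0.9898 + 0.4208)² / 0.01 ≈ 199.

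This does not give 55. The gap is a separate issue and does not enter the error-rate calculation. It matters here only through power:

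power at 55 per arm = Φ[(0.10 × √55 − 0.9898) / 0.5] = Φ(−0.496) ≈ 31%.

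So under the plan's own effect, EAD is non-significant about 100 − 31 = 69% of the time.

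**2. Error rate if either outcome may count.** With no true effect on either outcome:

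P(at least one P<.05) = 1 − P(|Z₁| < 1.96 and |Z₂| < 1.96), with (Z₁, Z₂) bivariate normal with correlation ρ.

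For ρ = 0 this is 1 − 0.95² = 9.75%.

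| ρ | At least one false positive |
|---|---|
| 0 | 9.75% |
| 0.3 | 9.5% |
| 0.5 | 9.1% |
| 0.6 | 8.75% |
| 0.7 | 8.35% |
| 0.8 | 7.8% |
| 0.9 | 7.0% |

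For two exact 5% tests in this model, independence is the worst case. The Bonferroni bound is 10%.

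**3. Check with the article's types of test.** The simulation used 55 per arm, a chi-squared test on a binary EAD, a t-test (equivalent to ANOVA with two groups) on a correlated continuous score, and 100,000 runs per setting. With the score perfectly tied to the variable underlying EAD, the rate was 8.55% at a common EAD rate of 15% and 8.35% at 20%. The test statistics then correlated at only 0.65 and 0.70, because cutting a continuous variable into yes/no limits the correlation. With no correlation the rates were 9.7% and 10.0%; the second slightly exceeds 9.75% because the chi-squared test itself ran at 5.1%.

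**4. The other two readings.** If both outcomes must be significant, the joint false-positive rate cannot exceed 5%. If EAD alone is primary, its test stays at 5%. Only the either-one reading inflates the rate, and the article does not say which reading applies.

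**The case against.** The strongest objection is that no inflated error rate is established. The primary-outcome section says only that the two measures will be analysed; it does not say that either one makes the trial positive. The sample-size section attaches alpha to EAD alone, and on that reading nothing is inflated. A journal article may also leave testing order and multiplicity to a fuller document that is not shown.

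Much of this stands. The size is conditional, and the lack of a multiplicity method would not by itself be a finding. The conflict between the two sections remains, because the article itself fixes the choice of primary outcome and does so in two different ways.

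A reader might infer two stronger claims, and the documents support neither:

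- **That the liver error rate approaches 10%.** That is the value for independent tests, the least plausible case for outcomes sharing three laboratory inputs.
- **That the interim looks raise it to about 18–19%.** Preliminary Analyses does plan "two interim analyses on the data from the first 7 posttransplant days". But that figure needs L-GrAFT to be tested at each look, and a day 1–10 score cannot be computed from 7-day data. The section also gives the purpose as monitoring procedures, states no efficacy test at P<.05 at those looks, and does not say that the 60 and 160 patients are liver recipients. Not including L-GrAFT in an interim analysis is no error either.

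**Conclusion.** The point holds as an unreconciled primary designation, and it should be corrected. Liver Transplant Primary Outcome and Sample Size Calculation name different primaries, one unadjusted P<.05 applies throughout, and the conclusion is undefined if EAD and L-GrAFT disagree.

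The size is conditional on either outcome being allowed to count as success. The false-positive rate is then about 8–9% for assumed correlations of 0.8 to 0.5, against a stated 5%. Confidence is high that the sections conflict and moderate on the exact size, because the correlation is an assumption. These figures are for a single final analysis.

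**What to change.** Reconcile the two sections by amending the primary-outcome text, for example: *The primary outcome of the liver trial is the EAD rate, tested two-sided at .05. L-GrAFT is the first key secondary outcome; it is tested at .05 only if EAD is significant and is otherwise reported as an estimate with a 95% confidence interval.*

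With no true effect on either outcome, a false positive then requires EAD to be significant first, so the rate stays at 5%.

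**Cost.** One sentence, through the amendment route in Ethical Review, and no loss of power for EAD. The downside is that L-GrAFT alone cannot make the trial positive. With EAD power near 31%, L-GrAFT would reach a formal test only about that often under the assumed effect.

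**Alternatives.** Both are dearer:

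- Splitting alpha to .025 each cuts EAD power at 55 per arm to Φ[(0.7416 − 2.2414 × 0.505) / 0.5] ≈ 22%, and 80% power would need 242 per arm.
- Requiring both outcomes to be significant also holds the error rate, but its power cannot exceed the 31% for EAD alone.

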### Tissue and Vascular Morphology

Tissue injury is evaluated using histopathological analysis before and after ex vivo organ perfusion. Biopsy samples are taken during organ retrieval to assess graft suitability, after graft reperfusion into the recipient, and at the end of the transplant. Pretransplant biopsies are obtained according to our center practice. All tissue samples are sent to Bologna Transplant Center to reduce interlaboratory bias in preparing the slides.

For the livers, parenchymal and vascular damage are evaluated. For the kidneys, glomerular, vascular, tubular, and parenchymal damage are evaluated. Tissue samples are examined by two double-blind pathologists, who grade any damage from moderate to severe.

In addition, we perform immunohistochemical assays to investigate endothelial and epithelial cell injury, ischemia- reperfusion damage, the pro-inflammatory and anti- inflammatory environment, growth factors, dedifferentiation, repair, and apoptosis using specific stainings. Electron microscopy is performed to assess the features of oxidative injury, focusing on preservation of epithelial mitochondria, endothelial cells of the glomerular and peritubular capillaries, and liver sinusoids.

Tissue and perfusate samples are collected and coded to guarantee privacy and data protection in accordance with EU regulations. Perfusate and tissues samples collected for RT-PCR are snap-frozen and stored at –80°C. Tissue collected for immunohistochemical assays are preserved in glutaraldehyde solution.

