### Data Management

Demographic, clinical, and biological data of donors and recipients are collected and prospectively entered in the database. The data registration is anonymous, and a study identification code is assigned to each transplant, in accordance with the Helsinki Declaration.

Missing values are handled properly by the researchers to achieve accurate inferences about the data during the analyses of the results.

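### L-GrAFT, named under the liver primary outcome, falls under an unadjusted ANOVA or Kruskal-Wallis rule; a prespecified model with the randomization stratum and pre-transplant laboratory values may be more efficient at almost no cost

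*Protocol article*

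**What the plan says.** Four places in the protocol article bear on this.

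- **Liver Transplant Primary Outcome.** L-GrAFT stands next to EAD: "The rate of EAD and the Liver Graft Assessment Following Transplantation (L-GrAFT) risk score [16,17] will be analyzed". The score is "calculated from the peak AST level, bilirubin levels, platelet counts, and international normalized ratio values from days 1 to 10" after transplantation. All four inputs are post-transplant measurements.
- **Statistical Tests.** One rule covers all continuous outcomes: "The continuous variables will be compared using parametric (ANOVA) or non-parametric (Kruskal-Wallis) tests according to the data distribution". No covariate is named. The only multivariable method is given in one sentence: "Multivariate analysis will be performed using forward stepwise logistic regression analysis". That sentence names neither the outcomes nor the candidate covariates.
- **Randomization.** Liver recipients are stratified by whether the graft has more or fewer than 5 extended-criteria features. The Statistical Tests section does not mention this factor.
- **Data Management.** "Demographic, clinical, and biological data of donors and recipients are collected and prospectively entered in the database". Pre-transplant bilirubin, INR and platelet count are not listed by name.

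The Sample Size Calculation section rests on EAD, DGF, PNF and length of stay. It gives no effect size, SD or power for L-GrAFT.

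**The concern.** L-GrAFT is the only continuous measure under the liver primary outcome, so it is where covariate adjustment is simplest. Two kinds of information known before treatment could reduce its unexplained variance.

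The first is the stratification factor. It was presumably chosen because it was thought to predict outcome. If it does, leaving it out of the analysis keeps between-stratum variation in the error term although randomization has already balanced it.

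The second is the recipient's own laboratory state. Bilirubin, INR and platelet count, three of the four score inputs, can also be measured just before transplantation. If those values predict the day 1 to 10 values, part of the spread in L-GrAFT existed before HOPE or SCS could act.

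As written, the plan uses neither. Logistic regression does not fill the gap, because it needs a binary outcome. Forward stepwise selection also leaves the choice of covariates to the data. At stake are the width of the confidence interval for L-GrAFT and the chance of detecting a real effect with 55 livers per arm.

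**Working it through.** **Inputs from the document.** 55 livers per arm, 1:1 allocation, two-sided alpha .05 (Study Design; Sample Size Calculation).

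**Assumed inputs.** A true L-GrAFT difference of d = 0.5 SD, with 0.4 SD as a second case. R², the share of within-arm L-GrAFT variance explained by the covariates, is varied from 0 to 40%. The document gives neither. There is also no L-GrAFT power figure of the plan's own to reproduce.

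**Step 1, unadjusted.** Two-group ANOVA is equivalent to the two-sample t test. The noncentrality is d × √(n/2) = 0.5 × √27.5 = 2.622, with 108 df and critical value 1.982. Power is 73.8%. For d = 0.4 the noncentrality is 2.098 and power is 54.7%.

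**Step 2, adjusted.** The residual SD is multiplied by √(1 − R²), so the noncentrality becomes 2.622 / √(1 − R²). Three covariates leave 105 df, with critical value 1.983. The equivalent unadjusted size per arm is 55 / (1 − R²).

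| R² | SE multiplier | Noncentrality (d = 0.5) | Power, d = 0.5 | Power, d = 0.4 | Equivalent n per arm |
|---|---|---|---|---|---|
| 0 | 1.000 | 2.622 | 73.8% | 54.7% | 55 |
| 1% | 0.995 | 2.635 | 74.3% | 55.1% | 56 |
| 4% | 0.980 | 2.676 | 75.5% | 56.4% | 57 |
| 10% | 0.949 | 2.764 | 78.2% | 59.1% | 61 |
| 25% | 0.866 | 3.028 | 85.1% | 67.0% | 73 |
| 40% | 0.775 | 3.385 | 91.8% | 76.5% | 92 |

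**Step 3, a fourth covariate.** Adding the stratum gives 104 df. At d = 0.5 no power in the table moves by more than about 0.01 percentage points.

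**Step 4, the downside.** The table charges only for lost degrees of freedom. Chance imbalance in three useless covariates also inflates the variance, on average by about 3 / (110 − 6) = 2.9%. At R² = 0 the noncentrality is then about 2.622 / √1.029 = 2.585, and power is between 72% and 73% instead of 73.8%. On that reckoning adjustment breaks even at an R² of about 3%. The stratum adds almost nothing to this cost, because stratified randomization keeps it close to balanced.

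**Step 5, dropout.** At 50 per arm, roughly the plan's 10% upper dropout figure, d = 0.5 gives 69.7% unadjusted and 81.5% at R² = 25%.

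**The case against.** The strongest objection is that nothing here is an error. An unadjusted comparison of randomized arms is valid, and chance baseline imbalance does not invalidate it. The Statistical Tests section is a short general summary in a journal article, it does not mention L-GrAFT, and a fuller protocol or analysis plan may list covariates. This stands in part. The point is about efficiency, and a reader should not infer that the test is biased or that an adjusted analysis has been ruled out. Still, the article does not leave the method open. It names a test for all continuous variables and one type of regression, and neither adjusts L-GrAFT.

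A second objection is that L-GrAFT has no baseline. Its inputs are measured with the new liver in place, while pre-transplant values describe the native liver and are only proxies. This also stands. Adjustment does not need a baseline on the same scale, only covariates that predict the outcome, but how well these predict it is unknown. A reader might infer that precision is certainly being lost. The document does not support that: it gives no correlation and no recipient laboratory data, and the gain at an R² of a few percent is negligible.

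A third objection is that the pre-transplant values may not be in the database. The Data Management section makes it plausible that they are but does not name them. The fix therefore has to be conditional for those three covariates. The stratification factor is known for every randomized liver.

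It is also tempting to extend the argument to histology, with the retrieval biopsy as a covariate for the post-reperfusion biopsy. The document does not carry that. Tissue damage is graded, so the variance calculation above does not apply to it. Pretransplant biopsies follow center practice, so their availability for every graft is unknown.

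**Conclusion.** The point holds as an inexpensive improvement. The stated rule leaves L-GrAFT unadjusted, ignores the liver stratum, and names no adjusted method suited to a continuous score.

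The size of the gain is open. For a 0.5 SD difference with 55 per arm, power rises from 73.8% to about 78% if R² is 10%, 85% if 25% and 92% if 40%. It hardly changes if R² is 0 to 4%. These figures rest on assumed effect sizes and R² values, an approximately normal score and complete data.

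The possible gain is clearly larger than the possible loss, which is a few degrees of freedom and at worst about one percentage point of power. The sample size does not rest on L-GrAFT, so adjustment neither repairs nor weakens the stated power basis for EAD.

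**What to change.** State in the analysis plan that L-GrAFT is compared by a linear model, or the same model on ranks if the score is skewed, with these terms fixed in advance:

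- study arm;
- the liver stratum as used at randomization;
- where recorded among the recipient data, the last pre-transplant bilirubin, INR and platelet count, log-transformed where skewed.

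Report the adjusted difference with its 95% CI. Keep the ANOVA or Kruskal-Wallis comparison as supportive. Do not use stepwise selection for this outcome.

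First confirm that the three laboratory values are in the database. If they are not, keep arm and stratum only. Because the trial is open-label and already recruiting, date the change and make it before anyone examines L-GrAFT by arm.

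The cost is plan wording and up to four degrees of freedom. No added patients, samples or visits are needed if the values are already recorded.
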